## **9.4 Safety Oversight (Independent Safety Monitor plus SMC)**

A qualified and experienced physician not otherwise associated with this protocol will serve as the Independent Safety Monitor (ISM) at the site for this study as per the specifications set forth in the DMID standard operating procedures. The ISM's *curriculum vitae* will be maintained on record. If safety concerns are identified, the ISM may request a meeting of the SMC to review safety data. The ISM will also review all serious adverse events and provide an unbiased written report of the event within 10 calendar days of the initial report. At a minimum, the ISM will comment on the outcomes of the SAE and relationship of the SAE to the study product. The

ISM will also indicate whether he/she concurs with the details of the report provided by the study investigator.

Furthermore, the ISM, a licensed physician, with relevant expertise will have the primary responsibility to provide independent safety monitoring in a timely fashion. The ISM will review SAEs and other adverse events as needed and provide an independent assessment to DMID. The ISM may be a member of the SMC or may not be a member of the SMC but attends the open session of the meetings.

An SMC will be assembled to review the safety data as they are collected. The SMC meets the specifications set forth in the DMID standard operating procedures. The SMC will convene and make recommendations on dosage escalation, based on the safety data collected 14 days after the initial dose of the prior dosage level. The safety data will be compiled by The EMMES Corporation. Based on the recommendations of the SMC, the decision will be made regarding dosage escalation.

***Ad Hoc Meetings of SMC:*** The SMC may convene an *ad hoc* meeting to discuss any issue of safety raised by an investigator, the sponsor, or a member of the SMC. At the discretion of the investigators, the sponsor and SMC members, a non-serious AE that is:

- 1) Associated with the product
- 2) Does not meet the stopping rules criteria

may be considered as a trigger for an *ad hoc* SMC meeting to assess the safety of the product, without resulting in halting the enrollment of the trial or further vaccinations.

Furthermore, meetings and roles and responsibilities of SMC are described in study Charter. Please note that an OM will precede the study.

## **10 CLINICAL MONITORING**

### **10.1 Site Monitoring Plan**

Site monitoring will be conducted to ensure that human subject protection, study procedures, laboratory procedures, study intervention administration, and data collection processes are of high quality and meet sponsor, GCP/ICH, and regulatory guidelines, and that the study is conducted in accordance with the protocol and sponsor standard operating procedures. DMID, the sponsoring agency, or its designee will conduct site-monitoring visits as detailed in the monitoring plan or in the Manual of Procedures.

Site visits will be made at standard intervals as defined by DMID and may be made more frequently as directed by DMID. Monitoring visits will include, but are not limited to, review of regulatory files, accountability records, CRFs, informed consent forms, medical and laboratory reports, and protocol compliance. Study monitors will meet with investigators to discuss any problems and actions to be taken and document visit findings and discussions.

## 11 STATISTICAL CONSIDERATIONS

### 11.1 Study Overview

The primary objective of the study is to assess the safety and reactogenicity of ascending dosages of Adenovirus Type 35 Based circumsporozoite malaria vaccine among healthy subjects given in 3 intramuscular doses at 0, 1 and 3 months. The secondary objective of the study is to evaluate the immunogenicity of the Adenovirus Type 35 based circumsporozoite malaria vaccine through performance of humoral immune assays (ELISA for Ab vs. CS and Adenovirus Neutralization Assay for neutralizing Ab against Ad35) and cellular immune assays.

The primary outcome measure is the frequency and severity of injection site and systemic AEs. These variables will be analyzed descriptively by:

1. The number of subjects experiencing severe (Grade 3) injection site reactions within 14 days following vaccination.
2. The number of subjects experiencing severe (Grade 3) systemic reactions within 14 days following vaccination.
3. The number of subjects with severe or life-threatening adverse reactions considered associated with the vaccination at any point during the study period.

The secondary outcome measures are:

1. Antibody titers against the malaria circumsporozoite antigen at days 0, 28, 56, 84, 112 and 140 (Geometric Mean Titer and individual log ELISA units).
2. Neutralizing antibody titers against Adenovirus type 35 by Adenovirus Neutralization Assay at days 0, 28, 56, 84, 112 and 140.

The exploratory outcome measures are:

1. T cell responses against the malaria circumsporozoite antigen by Elispot.
2. T cell responses against the malaria circumsporozoite antigen by Flow Cytometry
3. Cytokine responses against the malaria circumsporozoite antigen by ELISA after whole blood stimulation.

We propose to confirm the safety of the new vaccine by assessing safety and reactogenicity of the vaccine at 14 days after the initial dose in the lower dosages before escalating to the next

dosage level. Dosage level groups will include 10 subjects given vaccine and 2 subjects given normal saline placebo control intramuscularly.

### **Sample Size Considerations**

The sample size of 10 per group is selected to obtain preliminary safety information on a small cohort of subjects before proceeding to larger trials. If there are adverse events associated with vaccination in this population, this study will have approximately 80% probability to observe at least one such event in a study size of 10 if the true rate is 10%. If there are no adverse events associated with the vaccine, the upper bound for the one-sided 95% confidence interval will be 18% for a study size of 10. The proposed sample size will provide pilot data on secondary outcomes and will not assure adequate power to reject secondary hypothesis of dose-related immunogenic response unless that response is very large.

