### **2.1.2 Clinical Experience**

A Phase 1 randomized, controlled, dosage-escalation trial to evaluate the immunogenicity, safety and reactogenicity in healthy adults 18 to 45 years of age is ongoing in the U.S. Seventy two subjects are randomized in a 5:1 ratio to receive vaccine or normal saline placebo control by the IM route at 0, 1 and 6 months. Fifteen subjects have received vaccine at  $10^8$  vp/mL, 15 subjects have received vaccine at  $10^9$  vp/mL, and 15 subjects have received vaccine at  $10^{10}$  vp/mL. Enrollment of subjects receiving vaccine at  $10^{11}$  vp/mL is ongoing.

One SAE, not associated with vaccination, has been reported; it was a small bowel obstruction related to appendectomy for appendicitis. It resolved without sequelae.

All mild and moderate AEs associated with injection resolved without sequelae. A causal association with vaccine cannot be determined, and the safety data have not been unblinded at this time. There were a total of 5 moderate AEs in 4 subjects associated with time of injection: a right sided paresthesia lasting 24 hours, itchy tongue which resolved, brachial plexopathy lasting 24 hours, anemia (iron deficiency) and diaphoresis which resolved the same day.

In the current ongoing study in the U.S., after evaluation of the first 6 participants of Group  $10^{11}$  vp/mL, it was noted that significant reactions (grade 3) occurred in 2 of the 6 and were considered associated with injection. Symptoms began in the first 8 hours following vaccination, but none occurred in the first 4 hours following vaccination. These symptoms included fever, chills, myalgia, nausea and GI side effects such as diarrhea, that occasionally lasted for several days, was self-limited, and may or may not have been related to the vaccine.

Two individuals, one from Group  $10^8$  vp/mL and one from Group  $10^{11}$  vp/mL, developed Grade 2 signs and symptoms consistent with a brachial plexus neuropathy that was deemed associated with vaccination. For the subject in Group  $10^8$  vp/mL, symptoms began on the day of vaccination for both the 2nd and 3rd vaccinations but resolved within 24 hours without sequelae. For the subject in Group  $10^{11}$  vp/mL, symptoms began within the first week after 2nd vaccination and were resolved by the Day 7 physical examination. Both of these events resolved without sequelae.

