### 5.2 Enrollment Within Each Dosage Cohort

This study will be performed as a randomized, double-blinded, dosage-escalation study. The first dosage cohort consists of 12 subjects: 10 will receive the Ad35.CS.01 malaria vaccine while 2 will receive placebo control product. The subjects in the first cohort will be enrolled as follows: subject #1 followed by subject #2 with a minimum of a 30 minute waiting period between vaccinating subjects. This schedule will allow for assessment of immediate reactions of subject #1 prior to vaccinating subject #2. Following enrollment of subject #2, a minimum of a 2-day waiting period will be required prior to enrollment of the next four subjects. This schedule will allow for further reactogenicity assessment. The minimum 2-day waiting period will continue between each group of four subjects until the enrollment of 12 subjects into the first cohort has been met.

Following the SMC review of 14-day safety data of the first cohort, the second dosage cohort will contain 12 subjects (10 will receive Ad35.CS.01 and 2 will receive normal saline placebo control product). Six subjects will be enrolled, followed by a minimum of a 2-day waiting period before the next six subjects will be enrolled. The minimum 2 day waiting period will continue between each group of six subjects until the enrollment of 12 subjects into the second cohort has been met. This process will be repeated for the third and fourth cohorts.

Enrollment of additional subjects within any dosage cohort will not occur if a halting rule is met. Enrolled subjects who drop out of the study for any reason will not be replaced.

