## **11.2 Final Analysis Plan**

The primary analysis will be conducted on data and samples collected through study day 140 of the last dosage cohort. Once the data are frozen for the primary analysis, subjects will continue to be followed in an unblinded manner for additional SAE surveillance in the Ad35.CS.01 recipients as indicated in the protocol. This additional information will be appended to the study report. This study, like other Phase I studies, is exploratory rather than confirmatory; its purpose is to estimate event rates and patterns of immune responses rather than to test formal statistical hypotheses. Estimates will be presented with their 95% confidence intervals. Descriptive approaches will be used to meet the protocol objectives as stated in this protocol. Results will be presented in tabular format, as well as graphically when appropriate. Formal comparisons between vaccine and placebo groups will not be made. For the purposes of collecting pilot data and planning of potential future trials, some comparisons of secondary outcomes may be made with the control groups, although the study is not powered to detect small to moderate differences.

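### Both sample-size figures are wrong for 10 vaccinees per dose group: about 80% should be 65%, and 18% should be 26%

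*Protocol*

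**What the plan says.** The sample-size rationale is one paragraph, Sample Size Considerations, within Protocol Section 11.1. It sets the group size: "The sample size of 10 per group is selected to obtain preliminary safety information on a small cohort of subjects". It then makes two numerical claims, each tied to that size.

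- Detection: "approximately 80% probability to observe at least one such event in a study size of 10 if the true rate is 10" percent.
- Precision when no events are seen: "the upper bound for the one-sided 95% confidence interval will be 18% for a study size of 10".

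The group size is stated consistently elsewhere. Section 11.1 says "Dosage level groups will include 10 subjects given vaccine and 2 subjects given normal saline placebo control intramuscularly", and the tables in the Protocol Summary and Section 4, with the text of Section 5.2, give the same 10 vaccine and 2 placebo subjects per cohort. Section 11.2 describes the trial as exploratory and estimation-based and adds: "Estimates will be presented with their 95% confidence intervals".

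**The concern.** Group size, event rate, confidence level and sidedness are all printed, so both results can be checked directly, and neither comes out. This is not a detail left to a statistical analysis plan, because the protocol itself prints the results.

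The paragraph is the protocol's only quantitative justification for 10 vaccinees per dose level, and safety is the primary objective. In a trial meant to estimate event rates, stated precision takes the place of a power calculation. Dose escalation is decided cohort by cohort (Sections 5.2, 9.4 and 15.4), so the per-group figure is the relevant one. Anyone approving the protocol is given too favourable a view of what an event-free group of 10 would show.

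**Working it through.** **Inputs**

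- Vaccinees per dose level: n = 10 (Sections 4, 5.2 and 11.1).
- True event rate: p = 0.10 (Sample Size Considerations).
- Interval: one-sided 95%, zero events (Sample Size Considerations).
- Dropout: none assumed, which favours the printed figures. Section 5.2 says "Enrolled subjects who drop out of the study for any reason will not be replaced".

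**Attempt to reproduce the printed figures at n = 10**

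Probability of at least one event: 1 − (1 − p)^n = 1 − 0.9^10 = 1 − 0.3487 = 0.6513. The protocol prints about 0.80.

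Exact (Clopper-Pearson) one-sided 95% upper bound with 0/n events: 1 − 0.05^(1/n) = 1 − 0.05^(1/10) = 0.2589. The protocol prints 0.18.

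Neither figure is reproduced.

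**Other readings of n**

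| n | Interpretation | P(at least one event), p = 0.10 | One-sided 95% upper bound, 0/n |
|---|---|---|---|
| 10 | vaccinees per dose level | 65.1% | 25.9% |
| 12 | whole cohort including placebo | 71.8% | 22.1% |
| 15 | vaccine group size in the US trial | 79.4% | 18.1% |
| 16 | next integer | 81.5% | 17.1% |
| 40 | all vaccinees | 98.5% | 7.2% |
| – | printed in the protocol | about 80% | 18% |

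Of these, only n = 15 matches both figures to the rounding used. Solving for n gives the same answer: 80% detection at a 10% rate needs ln(0.2)/ln(0.9) = 15.3 subjects, and an 18% bound needs ln(0.05)/ln(0.82) = 15.1. Section 2.1.2 reports groups of this size in the US trial ("Fifteen subjects have received vaccine at" each of three dose levels). It also says "Seventy two subjects are randomized in a 5:1 ratio to receive vaccine or normal saline placebo control", which over four dose levels gives 72 × 5/6 ÷ 4 = 15.

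**Other interval methods for 0/10**

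- One-sided 90% exact: 20.6%
- One-sided 95% Wilson: 21.3%
- One-sided 95% with uniform prior: 23.8%
- One-sided 95% Agresti-Coull: 24.9%
- Rule of three: 30%
- One-sided 95% Jeffreys: 17.1%

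Only the Jeffreys limit comes within 2 points of 18%. It does not round to 18%, the protocol does not name it, and no choice of interval method can repair the 80%.

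**What the printed figures mean at n = 10**

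- 80% detection needs a true rate of 1 − 0.2^(1/10) = 14.9%, not 10%.
- An 18% upper bound after 0/10 carries one-sided confidence of 1 − 0.82^10 = 86.3%, not 95%. A true rate of 18% would still give no events in 13.7% of such groups.
- The chance of missing a 10% event is 0.9^10 = 34.9%, against an implied 20%.

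**Supplement.** Section 11.2 does not give the sidedness of the reported 95% intervals. If they are two-sided and exact, the upper limit for 0/10 is 1 − 0.025^(1/10) = 30.8%. This is a different quantity from the one-sided bound and is not the measure of the error.

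**The case against.** The arithmetic has no good defence: the paragraph fixes n at 10 for both figures, and the word approximately cannot cover a 15-point gap. The fair objections concern consequence and scope.

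- **No decision rule uses these figures.** Escalation rests on committee review of 14-day safety data. Halting under Section 9.3 is triggered mainly by events in one or two subjects, by any new neurologic symptoms, or by judgement. Section 11.2 plans no formal vaccine–placebo comparison, and the reported intervals would be computed from the observed data. This stands. The protocol nowhere says the safety committee would read a clean cohort against the 18%, so the harm is to the design justification and not to any test or stopping boundary.
- **Some assurance remains.** The paragraph claims only preliminary information, and 65% and 26% are still informative. This also stands. What is missing is the assurance as printed.
- **Carry-over from the US trial is an inference.** The numerical match at 15 is exact to rounding, but the protocol gives no source. The error does not depend on the explanation.
- **Pooling all 40 vaccinees would look better.** It would, at 98.5% and 7.2%, but pooling assumes one event rate across doses from 10^9 to 10^11 vp/mL. Section 2.1.2 makes that doubtful, with grade 3 reactions in 2 of the first 6 participants at the highest dose in the US trial. The protocol makes no pooled claim, and the correction should not introduce one.

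**Conclusion.** The point holds. For 10 vaccinees per dose level, the probability of at least one event at a true rate of 10% is 65.1%, not about 80%. The exact one-sided 95% upper bound with no events is 25.9%, not 18%. The like-for-like errors are about 15 and 8 percentage points. Detection rests on independent binomial events with all 10 vaccinees evaluable; the bound also rests on the exact interval. Any unreplaced dropout would widen both gaps. No test, decision rule or enrolment number is invalidated, but the sole numerical rationale for the group size is wrong under the primary objective and must be corrected.

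**What to change.** Replace the two sentences in Sample Size Considerations with wording to this effect: with 10 vaccinees per dose level there is a 65% probability of observing at least one event if the true rate is 10% (80% if the true rate is about 15%); if no events are observed, the exact one-sided 95% upper bound is 26%. If the intervals under Section 11.2 are to be two-sided, add that the corresponding exact upper limit is 31%, labelled as such. Name the interval method so that the figure can be checked.

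The cost is a wording change in one paragraph and less favourable figures. Enrolment, visits and analyses stay as they are. If the sponsor intended about 80% and 18% as design targets, the alternative is to justify a group size of about 15 to 16 vaccinees, which is a design change and not a correction.

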## **11.2 Final Analysis Plan**

The primary analysis will be conducted on data and samples collected through study day 140 of the last dosage cohort. Once the data are frozen for the primary analysis, subjects will continue to be followed in an unblinded manner for additional SAE surveillance in the Ad35.CS.01 recipients as indicated in the protocol. This additional information will be appended to the study report. This study, like other Phase I studies, is exploratory rather than confirmatory; its purpose is to estimate event rates and patterns of immune responses rather than to test formal statistical hypotheses. Estimates will be presented with their 95% confidence intervals. Descriptive approaches will be used to meet the protocol objectives as stated in this protocol. Results will be presented in tabular format, as well as graphically when appropriate. Formal comparisons between vaccine and placebo groups will not be made. For the purposes of collecting pilot data and planning of potential future trials, some comparisons of secondary outcomes may be made with the control groups, although the study is not powered to detect small to moderate differences.

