## PROTOCOL SUMMARY

**Title:** A Phase 1 Randomized, Controlled, Double-Blinded, Dosage-Escalation Trial to Evaluate the Immunogenicity, Safety, and Reactogenicity of an Adenovirus Type 35 Based Circumsporozoite Malaria Vaccine in Burkina Faso, Semi-Immune, Healthy Adults 18 to 45 Years of Age.

**Phase:** I

**Population:** 48 healthy male and female subjects aged 18 to 45 years in Burkina Faso.

**Site:** Projet de Développement de Vaccins Anti-Paludique- Centre National de Recherche et de Formation sur le Paludisme (PDVAP/CNRFP) Burkina Faso

**Study Duration:** Approximately 12 months per subject .

**Description of Agent or Intervention:** Adenovirus Type 35 Circumsporozoite Malaria Vaccine (Ad35.CS.01) versus Normal Saline Placebo Control via Intramuscular Injection.

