### **3.2 Study Outcome Measures**

#### **3.2.1 Primary Outcome Measure**

- The number of subjects experiencing severe (Grade 3) solicited injection site reactions within 14 days following vaccination.
- The number of subjects experiencing severe (Grade 3) solicited systemic reactions within 14 days following vaccination.
- The number of subjects spontaneously reporting severe (Grade 3) adverse events considered associated with the vaccination at any point during the study period.
- Serious adverse events considered associated with the vaccination reported at any point during the study period.

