**7.3.21 Day 365 (+1 month), Visit 20**

- Subjects will be evaluated in the clinic. Vital signs (auxiliary temperature, blood pressure, pulse) will be assessed and recorded. Subjects will be interviewed regarding any potential risk behavior that would increase their chance of becoming infected with HIV virus.
- Any spontaneous AEs that have occurred since the last visit will be assessed.
- A targeted PE will be performed if indicated by the subject's interim medical history.
- Concomitant medications will be reviewed and updated, if applicable.
- A 5-mL blood sample will be collected for HIV testing.

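### Primary outcomes 3 and 4 run over about 12 months, but Section 11.2 analyses them at the Day 140 cut, unblinds later causality judgements and appends SAEs only

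*Protocol*

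**What the plan says.** Protocol Section 3.2.1, repeated in the Protocol Summary, lists four primary outcomes. The first two are solicited Grade 3 reactions within 14 days of a vaccination. The third is "The number of subjects spontaneously reporting severe (Grade 3) adverse events considered associated with the vaccination at any point during the study period". The fourth is "Serious adverse events considered associated with the vaccination reported at any point during the study period". The Summary gives the study duration as "Approximately 12 months per subject".

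Section 11.2 sets the analysis: "The primary analysis will be conducted on data and samples collected through study day 140 of the last dosage cohort". Once those data are frozen, "subjects will continue to be followed in an unblinded manner for additional SAE surveillance in the Ad35.CS.01 recipients as indicated in the protocol". Of what is gathered then, it says: "This additional information will be appended to the study report".

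Sections 7.3.18 to 7.3.21 schedule Visits 17 to 20 (Days 196 to 365) without distinguishing the arms, and Appendix A has no split by arm. The Day 365 visit includes "Any spontaneous AEs that have occurred since the last visit will be assessed" and "A 5-mL blood sample will be collected for HIV testing". Inclusion criterion 7 in Section 5.3 asks every subject to accept contact for one year about serious adverse events. Section 5.5.2 makes the pharmacist the only unblinded person and names no date on which the blind ends.

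**The concern.** For outcomes 3 and 4, attribution is part of the endpoint. Section 9.1.1 makes relationship a two-way judgement: associated needs a suspicion of a link with study product, a temporal relation, and no other explanation. An assessor who knows the allocation may judge the same illness differently in a saline recipient and in a recipient of the highest dosage. Section 5 describes intense seasonal malaria at the site, so late illnesses with a debatable cause are foreseeable.

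Section 11.2 therefore creates two problems. An outcome defined over a year is reported as primary on part of that year, and its later part is judged under a different blinding regime. The later surveillance also names only SAEs, so a non-serious Grade 3 event judged associated after the freeze counts toward outcome 3 by definition but has no place in either report. At stake is whether the reported counts for outcomes 3 and 4 are the quantities that Section 3.2.1 defines.

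**Working it through.** The plan gives no figure for the share of follow-up beyond the cut, so there is none to reproduce. The inputs are Day 140 (Section 11.2), Day 84 for dose 3 and Day 365 for the last visit (Section 7.3, Appendix A), and the enrolment waits and 14-day safety review (Section 5.2).

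**1. Last subject enrolled in cohort D.** Days after the cut: 365 − 140 = 225, and 225/365 = 61.6%. Days after dose 3: 365 − 84 = 281, of which 140 − 84 = 56 precede the cut. So 225/281 = 80% of follow-up after dose 3 lies outside the primary analysis.

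**2. All cohorts, calendar cut, fastest escalation the waits allow, no SMC delay (assumption).** Cohort A is enrolled as 2, 4, 4 and 2 subjects two days apart. Each later cohort starts 14 days after the previous cohort's last first dose and enrols 6 and 6. The cut falls at 54 + 140 = 194 days after the first subject's first dose.

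| Cohort | First-dose days | Follow-up at cut (days) | Days after cut | Share of 365 |
|---|---|---|---|---|
| A | 0, 2, 4, 6 | 194 to 188 | 171 to 177 | 47 to 48% |
| B | 20, 22 | 174 to 172 | 191 to 193 | 52 to 53% |
| C | 36, 38 | 158 to 156 | 207 to 209 | 57% |
| D | 52, 54 | 142 to 140 | 223 to 225 | 61 to 62% |

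Weighted by subjects, the person-days after the cut are 2,088 + 2,304 + 2,496 + 2,688 = 9,576 of 48 × 365 = 17,520, or 55%. Slower escalation lowers this.

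**3. Cut versus freeze.** Unblinding comes at the freeze, which is later than the cut. Visit 16 has a window of one month either way. A last visit near Day 170 leaves 195/365 = 53% unblinded for that subject. A further 30 to 60 days of data cleaning (assumption) leaves 165/365 = 45% to 135/365 = 37%.

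**4. Follow-up by dosage under a calendar cut.** Mean first-dose day is 3 in cohort A. With no SMC delay it is 53 in cohort D, so mean follow-up is 194 − 3 = 191 against 194 − 53 = 141 days, a ratio of 1.35. If each SMC review takes 7 or 14 days (assumption), the last cohort D subject is dosed on day 75 or 96 and the cut falls on day 215 or 236. The ratios are then 212/141 = 1.50 and 233/141 = 1.65.

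**5. Where each late event goes.**
- SAE judged associated, vaccine recipient: appended.
- SAE judged associated, placebo recipient: unclear from the wording.
- Non-serious Grade 3 event judged associated, either arm: neither report.
- Day 365 HIV result: after the cut for every cohort on these timelines.

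**The case against.** The strongest reply is that the trial is exploratory and descriptive, and Section 11.2 plans no formal comparison of vaccine with placebo. Outcomes 1 and 2 end around Day 98. Escalation uses 14-day data after the first dose. Neither is touched. This stands, and it limits the severity. It does not remove the point, because Section 11.2 gives estimation of event rates as the purpose, and an estimate can be distorted without any test.

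Section 9.1.1 says in one place that spontaneous events are collected for 14 days after vaccination, which might suggest that no late outcome 3 events exist. But Sections 7.3.18 to 7.3.21 assess spontaneous events at every late visit, Section 9.2 requires all events on study to be documented, and Section 3.2.1 sets no 14-day limit. These passages need reconciling too.

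For SAEs, the Independent Safety Monitor also comments on relationship and the SMC may do so, so the site investigator is not the only voice. The protocol does not say that either stays blinded after the freeze.

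A reader might go further, in four ways that the document does not support:
- *Placebo surveillance is dropped.* The same sentence in Section 11.2 says that subjects continue to be followed as the protocol indicates, and the protocol indicates Visits 17 to 20 for all. This is a contradiction in wording.
- *Unequal follow-up masks a dose-related increase.* All cohorts have three doses and about 56 days after dose 3 at the cut. Cohort A's extra time is later still, where temporally related events are less expected. The calendar reading itself is not certain, since study day is counted per subject in Appendix A. If the cut means each subject's own Day 140, the imbalance vanishes, but 62% of the window is then left out for everyone.
- *The HIV result is biased by unblinding.* Serology is a laboratory result, and the halting rule on a positive test needs no causality judgement.
- *A placebo event could never be judged associated.* Relationship is judged to study product, and Section 6.1 covers the saline placebo as well.

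**Conclusion.** The point holds in limited form and should be fixed. Outcomes 3 and 4 are defined over about 12 months, analysed as primary on part of that time, and judged unblinded for the remainder. The unblinded share is at most 62% for the last subject in cohort D. At the fastest escalation, at most 55% of all planned person-days fall beyond the cut. Both are maxima, and a later freeze lowers the unblinded share. Late non-serious Grade 3 associated events fall outside both described reports. These conclusions come from the text and need no assumption about event rates.

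The vaccine-recipient wording contradicts the visit schedule and the one-year contact criterion and must be reconciled; it is not evidence that placebo follow-up ends. The cohort A to D follow-up ratio, 1.35 with no SMC delay and 1.50 to 1.65 with assumed reviews of one to two weeks, applies only under a calendar cut. Its effect on event rates is not shown. The change should precede the freeze, because unblinding cannot be undone.

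**What to change.** Amend Section 11.2 in three places.

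1. **Blinding.** Limit treatment codes at the Day 140 analysis to the data coordinating centre and named sponsor staff. Keep subjects and site causality assessors blinded until the last Day 365 visit. At minimum, flag every relationship assessment made after unblinding and report it separately. Add the end of the blind to Section 5.5.2.
2. **Scope.** Replace the phrase confining later surveillance to vaccine recipients with a statement that all subjects in both arms are followed and reported to Day 365, for Grade 3 associated adverse events as well as SAEs. Align the spontaneous-event collection period in Section 9.1.1.
3. **Window.** At the first analysis, report outcomes 3 and 4 on a common window ending at each subject's own Day 140, and list later events already observed so that no known safety information is withheld. Give the full-window result for both outcomes from the Day 365 data as the result for the outcomes as defined, rather than as an appendix of SAEs.

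The cost is protocol wording and an access-control step. No visits are added. Treatment codes reach the site later, outcomes 3 and 4 are tabulated twice, and their full-window result arrives up to 225 days after the Day 140 cut if visits keep to schedule.
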